## Abstract

**Introduction:**

People living with HIV/AIDS (PLWHA) have complex physical, psychological, social and spiritual needs following diagnosis and poorer health-related quality of life than the general population. Holistic assessment and care delivery incorporating person-centred principles is required to address these needs. This protocol describes a cluster randomised controlled trial (cRCT) and process evaluation to evaluate the effectiveness of the extra community-based enhanced care intervention (ExtraCECI) to improve the quality of life and person-centred outcomes for PLWHA in Ghana.

**Methods and analysis:**

This cRCT will randomly assign 26 recruited HIV clinics using 1:1 allocation to either ExtraCECI intervention or standard HIV care, with each clinic recruiting an average of 25 participants, that is, 650 in total. Eligible participants are adult PLWHA aged at least 18 years and in HIV care for at least 6 months, with cognitive ability to consent as guided by the Mental Capacity Act, clinically well to participate, attending an outpatient clinic. Healthcare professionals (HCP) at clinics randomised to the ExtraCECI intervention arm will receive training on person-centred care and holistic assessment of PLWHA in the domains of physical, psychological, social and spiritual well-being. PLWHA will be empowered to contribute to their care decisions including HCP using telehealth for ExtraCECI delivery with ongoing mentorship, while participants in the Standard HIV Care arm continue with usual care. The primary outcome is quality of life measured at the individual level using Medical Outcomes Study-HIV (MOS-HIV). The primary analysis will compare MOS-HIV total scores between groups using repeated measure linear mixed model and adjusting for important baseline characteristics (including stratification factors) and random effect of clinic. The incremental cost-effectiveness ratio will be used to estimate the cost-effectiveness of the ExtraCECI intervention, and a process evaluation will be conducted.

**Ethics and dissemination:**

This protocol was approved by Edinburgh Napier University School of Health and Social Care Research Integrity Committee (REF: SHSC3681836) and the Ghana Health Service Ethics Review Committee (GHS-ERC:010/07/24). Results from this study whether positive or negative will be presented to participating sites, communities, at scientific conferences and published in peer-reviewed journals.

**Trial registration number:**

ISRCTN77405303.

STRENGTHS AND LIMITATIONS OF THIS STUDYThe study will use a cluster randomised controlled design to evaluate the effectiveness of the extra community-based enhanced care intervention (ExtraCECI), this design minimises the risk of confounding factors influencing the results.The training component of the ExtraCECI intervention allows for the training of health professionals at the clinic level, building their capacity to continue to deliver person-centred care beyond study end.The 26 clusters being included in this study are in the Greater Accra Region of Ghana, thus extrapolating findings to other regions remains to be explored, however, with increased urbanisation; findings are likely to be relevant to other areas of Ghana.Due to the nature of the intervention, it is not possible to blind participants or researchers as this is a behavioural intervention and outcomes are self-reported.

## Introduction

 HIV/AIDS remains a condition of public health concern with approximately 39.9 million people living with HIV and about 30.7 million receiving antiretroviral therapy (ART) globally.^1^ Sub-Saharan Africa carries more than two-thirds of the global HIV burden. There are an estimated 330 000 people living with HIV in Ghana.^2^ People with HIV have complex physical, psychological, social and spiritual needs following diagnosis^3^ and poorer health-related quality of life (QoL) than the general population.^4^ Self-reported physical and psychological symptoms are associated with poorer ART adherence,^5^ sexual risk taking,^6^ viral rebound^7^ and poorer self-rating of health.^8^ In contrast, good psychosocial care and communication with HIV care providers are associated with improvements in clinical outcomes, adherence and retention in care.^9 10^ The Joint United Nations Programme on HIV and AIDS (UNAIDS) advocates for countries to adopt community-based approaches and to keep people living with HIV/AIDS (PLWHA) ‘healthy and alive through the delivery of person-centred and holistic care’.^11^ Task shifting and decentralising HIV services to community settings in low and middle-income countries (LMICs) have proven cost-effective,^12^ resulting in decreased HIV-related mortality, virologic failure and other adverse health outcomes.^13^,^16^

UNAIDS proposed person-centred care (PCC) as a fast-track action for its ‘95-95-95’ global strategy to improve rates of diagnosis, treatment adherence and viral suppression for PLWHA by 2030.^17^ With the 95-95-95 targets, Ghana currently stands at around ‘72-87-68’ for diagnosis, treatment and viral suppression, respectively.^18^ Respondents to this strategy, including HIV community representatives, advocacy groups and experts in the field, have also advocated for a fourth priority focusing on improved QoL.^19^ Greatest attention has been paid to viral suppression, at the expense of broader psychological, social and spiritual concerns that persist despite treatment advances.^6 20^ Care that addresses the multidimensional concerns of people with HIV requires a person-centred approach, a core principle of quality healthcare.^21 22^ Mezzich defined PCC as care ‘dedicated to the promotion of health as a state of physical, mental, social and spiritual well-being as well as to the reduction of disease and founded on mutual respect for the dignity and responsibility of each individual person’.^23^ Thus, PCC puts the individual at the centre of their care, helps individuals to access the care they need, when they need it, by involving them in their own care decisions.^24^ Such approaches have been found to improve patient experience, care quality and health outcomes.^25^ However, PCC is an approach that evolved in high-income settings, and there are limited data available to model contextually and culturally appropriate PCC in LMIC.^26^,^28^ A clinical trial in Kenya reported that the use of person-centred assessment and care delivered by trained healthcare professionals (HCP) to people with HIV on treatment had a positive effect on self-reported mental health-related QoL and psychosocial well-being.^29^

In order to generate evidence for feasible practice of PCC in Ghana, we followed the Medical Research Council (MRC) guidelines for developing and evaluating complex interventions^30 31^ to first identify the evidence of person-centred models of HIV care in community settings.^32^ Then using Mezzich’s definition as our theory of PCC,^23^ we explored what constitutes PCC for PLWHA and HCP as well as what outcomes matter to them.^33^ Findings from these studies informed the development of a community-based enhanced care intervention (CECI) to improve person-centred outcomes for PLWHA, which was tested in a feasibility cluster randomised controlled trial (cRCT).^34^ CECI feasibility testing achieved recruitment and retention rates with post-trial interviews reported good acceptability among PLWHA as well as highlighted important areas of refinement to CECI.^34^

### Aim and objectives

To conduct a cRCT to evaluate the effectiveness of a person-centred intervention for people with HIV (extra community-based enhanced care intervention; ExtraCECI) compared with standard HIV care in improving QoL and person-centred outcomes for PLWHA in Ghana.

### Objectives

To establish a patient and public involvement (PPI) person-centred network of PLWHA support groups and stakeholders to inform research procedures and dissemination throughout the project implementation.To refine the CECI by adding an extra component to become ‘ExtraCECI’ through a theory of change workshop.To evaluate the effectiveness of ExtraCECI to improve QoL and person-centred outcomes for PLWHA compared with standard HIV care.To assess the cost-effectiveness of ExtraCECI compared with standard HIV care and describe the implications for Ghana Health Services’ resource management.To conduct a process evaluation using quantitative and qualitative data sources to understand facilitators and barriers to implementation and identify what worked, for whom, why and in what circumstances.

## Methods and analysis

### Setting

This study will be conducted in community HIV clinics within the Greater Accra Region (GAR) of Ghana. The region has both urban and rural communities with a mixture of different socioeconomic, cultural and educational backgrounds. Of the 346,120 PLWHA in Ghana, about 76,730 PLWHA are in the GAR,^35^ with approximately 94 ART clinics and 506 HIV testing facilities. Eligible clinics provide similar HIV care services including provision of ART, care for key populations (men who have sex with men (MSM), sex workers and drug users), ART adherence, counselling, psychosocial and spiritual care.

### Establishment of patient and public involvement

We will work with community health workers, clinic staff and Models of Hope (PLWHA peer supporters) within the GAR of Ghana to identify community leaders of PLWHA advocacy and support groups. The Models of Hope are not available at some clinics however this project will recruit 20 PLWHA peer supporters to cover multiple clinics during the project implementation. Our public and PLWHA group will be drawn from these advocacy and support groups and will be engaged throughout the research processes from study inception, CECI refinement with associated study documents, project delivery and the interpretation of trial findings. The public and PLWHA group will also serve as an advisory group and will be provided with introductory training on research and the principles of PCC to enable them to effectively discharge their role.

#### Refining CECI to ‘ExtraCECI’

The CECI components include: (1) a training programme on person-centred communication, (2) holistic assessment of PLWHA’s symptoms and concerns in the domains of physical, psychological, social, and spiritual well-being using a structured tool, (3) a care plan to capture holistic needs to facilitate collaborative care planning and delivery, (4) regular support/mentorship for HCP with fidelity monitoring.

‘Extra’ components of: (1) empowering PLWHA on how to engage, participate and contribute to their care decisions; and (2) working with HCP and Models of Hope to use telehealth (text messaging for information sharing and voice calls for follow-up, assessment and enabling feedback in the communication process) for care delivery is being added to CECI as ‘extra’ components. These extra components of CECI will rely on collaborative discussion of PLWHA’s symptoms and concerns with the HCP to inform holistic care planning and delivery. Consideration has been given to these additional components, as both HCP and PLWHA have identified the need for PLWHA to be empowered to be able on to engage, participate in care consultations and contribute to care decisions.^34^ Working with HCP and Models of Hope to use telehealth to deliver CECI gives PLWHA more options to access care through telecommunication.

The process of refinement will include:

CECI Theory of Change (ToC) workshop with stakeholders including our public and PLWHA group members, where CECI will be presented with the mechanisms of action identified during the feasibility cRCT.The areas of refinement as identified as empowering PLWHA on how to engage, participate and contribute to their care decisions will be discussed with stakeholders for their views and input.Additionally, the ToC workshop will explore how to work with HCP and Models of Hope to use mobile phones^36^ to deliver CECI, since mobile phones (eHealth) have shown to be effective in delivering interventions to PLWHA in sub-Saharan Africa.^37^Share samples of the holistic assessment and care planning tools for CECI with stakeholders for review and input.

### ExtraCECI

Once the ‘Extra’ components of ‘empowering PLWHA to engage, participate and contribute to their care consultations and decisions’ and the use of telehealth have been added to CECI, the refined CECI will then be referred to as ExtraCECI. These extra components of empowering PLWHA will be incorporated at the clinic level pre-consultation meetings, where groups of PLWHA scheduled for their appointments usually have initial general discussions with HCP prior to having individual consultations. ExtraCECI aims to improve confidence levels of PLWHA to contribute meaningfully to their care decisions.

### Study design

We will conduct a cRCT to evaluate the effectiveness of ExtraCECI in HIV clinics within Ghana. A parallel group design with 1:1 allocation ratio will be utilised including an economic evaluation and an embedded qualitative process evaluation informed by the ‘Evaluation stage’ of MRC guidelines for developing and evaluating complex interventions.^30 31^ Recruitment and baseline (T0) data collection at each cluster will be conducted before randomisation and the start of any intervention delivery. The first care appointment following randomisation will be treated as time point T1, followed by 3-monthly follow-ups at 3-, 6-, 9- and 12 months recorded at T2, T3, T4 and T5. The cRCT will be reported according to the CONSORT statement^38 39^ and details of study recruitment and participation presented in a CONSORT flow diagram as in figure 1.

**Figure 1 F1:**
[figure not shown]
ExtraCECI study flowchart.

#### Inclusion and exclusion criteria

The study inclusion criteria for clinics, HCP and PLWHA are presented in table 1.

**Table 1 T1:** ExtraCECI study inclusion and exclusion criteria

Inclusion criteria	Exclusion criteria
HIV clinics Clinics with a minimum travel distance of 3 km apart to minimise treatment ‘contamination’^56^ between the intervention and control arms. The clinic lead must be willing to participate, be randomised and commit to compliance with ethics and study requirements. At least two HCP per clinic who meet the inclusion criteria (below) must be willing to participate at the time of clinic inclusion.	Clinics that are less than 3 km travel distance apart with potential for treatment contamination. Clinics not willing to participate in the study and/or not willing to comply with ethics and study requirements. Clinics with less than two HCP who meet the inclusion criteria at the time of clinic inclusion.
HCP HCP who regularly provide hands on care for PLWHA. HCP providing care for PLWHA in eligible clinics for at least 6 months. Willing to attend intervention training, mentorship and support sessions.	HCP not providing regular hands-on care to PLWHA. HCP providing care for PLWHA in eligible clinics for less than 6 months. Not willing to attend intervention training, mentorship and support sessions.
PLWHA Adults PLWHA from age 18 years. HIV positive diagnosis and in care for at least 6 months, to ensure that PLWHA has the experience of care to reflect on. PLWHA who have cognitive ability to consent as guided by the Mental Capacity Act. PLWHA who are clinically well to participate (having>200 cells/mm^3^ CD4 count/ viral load<200 without complications). PLWHA attending clinic for ART refill, adherence counselling, psychosocial and spiritual support, including other services targeted at PLWHA who are in care.	PLWHA under age 18 years. Diagnosed with HIV and in care for less than 6 months. PLWHA not having cognitive ability to consent. Having<200 cells/mm^3^ CD4 count or viral load>200, severe complications/ co-morbidities including cardiovascular diseases, malignancies, pneumonia and requiring specialised treatment at secondary/tertiary health facility). Persons attending clinic for pre-counselling & testing services including prevention of mother-to-child transmission.

### Participant screening consent and recruitment

HIV clinics within the Greater Accra Region of Ghana will be profiled based on their location, services provided and total number of PLWHA registered per clinic. Eligible clinics will be invited into the study with letters including the study information and consent forms. HCP within recruited clinics will initially screen potential participants and refer eligible participants to the researchers for further screening and study information discussion. Up to one week will be allowed for addressing questions from potential participants, and eligible participants who agree to take part in the research study will be asked to give informed consent by signing or thumb printing a consent form. This consent process will continue until the target number for each cluster (see the Site selection and randomisation section) is recruited. For those who provide informed consent to participate in the trial, their baseline data will be collected immediately or otherwise scheduled within one week of consenting for baseline data collection.

### Sample size

As there is no widely established minimal clinical important difference for the Medical Outcomes Study-HIV (MOS-HIV) measure, we followed best practice guidelines^40^ using a standardised effect size approach. We estimated that an average cluster would be 20, but there would be variation in this estimate, which we incorporated in the sample size (coefficient of variation).^41^ No clinic level intracluster correlation coefficient (ICC) is available, and the feasibility trial conducted was too small to reliably estimate the ICC, hence we chose a value of 0.04.^42^ Therefore, for 90% power to detect a minimum effect size of 0.4 in the MOS-HIV, a total of 650 PLWHA would need to be randomised from 26 clinics, assuming an ICC of 0.04, average cluster size of 25 with 20% loss to follow-up.

### Site selection and randomisation

The 26 HIV clinics recruited will be randomly allocated to either standard HIV care or ExtraCECI after baseline data collection and before intervention training for HCP using a restricted randomisation frame in three separate batches (6, 10 and 10 sites) in order to stagger recruitment and follow-up. A statistician from York Trials Unit will generate a randomisation frame consisting of a list of all possible combinations of allocating 26 sites to 2 arms using bespoke code in Stata V.18. The list of allowable combinations will be reduced by excluding combinations that do not correspond to a 1:1 allocation of sites within any batch. One combination will then be selected at random from the final restricted list. Allocation will only be communicated to sites once recruitment for the relevant batch is complete. See figure 1 for study flowchart.

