### Statistical and effectiveness analysis

Analyses will be undertaken in Stata V.18 (or later) based on two-sided 5% significance levels under the principles of intention-to-treat, as detailed in a statistical analysis plan. Baseline data will be summarised descriptively by treatment group using means and SD or median and IQR for continuous variables and counts and percentages for categorical variables. Participants' MOS-HIV scores will be analysed using a repeated measures linear mixed effects model. The model will include MOS-HIV scores as outcome, with fixed effect of treatment by time interaction, adjusting for important baseline variables (including stratification factors) and random effect of clinic. Time points will be nested within patients and modelled using a covariance structure. Different structures will be considered and the simplest structure with the best fit (assessed using Bayesian Information Criterion) will be used. Model assumptions of normality of standardised residuals will be assessed (using Q-Q plots) in addition to homoscedasticity (using a scatter plot of standardised residuals against fitted values). If the assumptions are not met, relevant transformations of MOS-HIV scores and non-parametric tests will be considered. The treatment effect at the time points will be extracted in the form of an adjusted mean difference, 95% CI and p value (with the primary being at 12 months). Analysis of the primary outcome will be checked by a second statistician in accordance with clinical trials unit SOPs (Primary Analysis Sign Off Form) before results are circulated to wider members of the trial team. Continuous secondary outcomes will be similarly analysed using a similar model to the primary analysis.

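### The restricted randomisation balances only clinic numbers within batch and leaves clinic location and size to chance, although both are profiled beforehand; a balance limit would be a cheap, modest improvement.

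*Protocol article*

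**What the plan says.** Site selection and randomisation describes the allocation of the 26 clinics "using a restricted randomisation frame in three separate batches (6, 10 and 10 sites) in order to stagger recruitment and follow-up". A statistician lists every way of dividing the sites between two arms. The list is then cut by one rule: "The list of allowable combinations will be reduced by excluding combinations that do not correspond to a 1:1 allocation of sites within any batch". The last step is: "One combination will then be selected at random from the final restricted list". No clinic characteristic appears in the procedure.

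Participant screening consent and recruitment says that the region's clinics are "profiled based on their location, services provided and total number of PLWHA registered per clinic", and eligible clinics are then invited, so location and size are on file before any allocation. On the region itself, Setting says: "The region has both urban and rural communities with a mixture of different socioeconomic, cultural and educational backgrounds".

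Statistical and effectiveness analysis specifies a mixed model "adjusting for important baseline variables (including stratification factors) and random effect of clinic".

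**The concern.** Listing all allocations, discarding the unacceptable ones and drawing from the rest is the machinery of covariate-constrained randomisation. Here it does no more than block by batch, because equal numbers within batch is the only test applied. With 13 clinics per arm, arms can easily differ in the share of rural clinics or in typical clinic size. If those features relate to quality of life, the imbalance adds chance error to the treatment effect and makes the baseline comparison harder to defend. The data and code needed to prevent this are already part of the plan.

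**Working it through.** **Inputs from the protocol article.** 26 clinics in batches of 6, 10 and 10, allocated 1:1 within batch (Site selection and randomisation); effect size 0.4, 90% power, ICC 0.04, 25 recruited per clinic, 20% loss (Sample size); two-sided 5% (Statistical and effectiveness analysis).

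**Assumptions, because the article gives no figures.** One continuous clinic covariate (such as log number registered), standardised across clinics; one binary factor held by 8 of 26 clinics (such as rural); the factors explain 25% to 50% of between-clinic variance. The coefficient of variation of cluster size is also not given.

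**1. The plan's own figure.** An effect of 0.4 SD at 90% power needs 132 per arm, 264 in all, under individual randomisation. With 20 analysed per clinic and an assumed coefficient of variation of 0.5, the design effect is 1 + ((0.25 + 1) × 20 − 1) × 0.04 = 1.96. Then 264 × 1.96 = 517.4, and 517.4 / 20 = 25.9, so 26 clinics; 26 × 25 = 650. The figure reproduces, and nothing below changes it.

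**2. Number of allocations under the batch rule.** C(6,3) × C(10,5) × C(10,5) = 20 × 252 × 252 = 1,270,080.

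**3. Chance imbalance, continuous covariate.** The SD of the arm difference is √(1/13 + 1/13) = 0.392. A normal approximation gives P(|difference| > 0.5 SD) = P(|Z| > 1.275) = 20%; simulating the 6/10/10 scheme gives 21%.

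**4. Chance imbalance, binary factor.**
- 8 of 26 clinics placed at random across batches: 6 v 2 or worse in 20% of draws.
- 8 of 26 spread 2/3/3 over the batches (exact within-batch hypergeometric): 282,240 of 1,270,080 = 22%.
- For comparison, 13 of 26 spread 3/5/5: 8 v 5 or worse in 45%, 9 v 4 or worse in 13%.

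At least one of the two imbalances (over 0.5 SD, or 6 v 2 or worse) occurs in about 37% of draws.

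**5. What a constraint adds to power.** With equal clusters of 20, a variance share f explained and perfect balance, SE = √[(2/13) × (0.04(1 − f) + 0.96/20)].
- f = 0: SE 0.116; power 90.9% (t, 24 df).
- f = 0.25: SE 0.110; power 93.8%.
- f = 0.50: SE 0.102; power 96.3%.

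Most of that rise comes from adjustment, not from the draw. To separate the two, allocations were simulated with a clinic-level model containing arm, batch and both covariates (26 − 6 = 20 df), with and without the limits in step 6:

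| Variance explained | Batch-only draw, adjusted | Constrained draw, adjusted | Gain |
|---|---|---|---|
| 25% | 91.0% | 92.9% | about 2 points |
| 50% | 94.1% | 95.6% | about 1.5 points |

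**6. Room left for randomness.** With limits of two clinics on the binary factor and 0.25 SD on the continuous one, applied across all 26 clinics, full enumeration for five random covariate sets left 432,236 to 491,510 allocations, which is 34% to 39% of 1,270,080. The same 0.25 SD limit applied inside the batch of 6 alone leaves a median of only 4 of its 20 allocations.

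**The case against.** Batch-stratified allocation is a valid design, and the article describes it completely. The treatment estimate is unbiased, type I error is intact, and between-clinic variation is already in the ICC used for the sample size. All of this stands. A reader might infer that the arms could be confounded with clinic type; the documents support only chance imbalance, which randomisation and the model allow for.

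Three other stronger readings are tempting and do not hold.

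- A covariate explaining half the between-clinic variance and imbalanced by 0.5 SD would shift an unadjusted effect by 0.5 × √0.5 × 0.2 = 0.07 SD, or 18% of the 0.4 target (0.2 being the between-clinic SD, √0.04). The plan does not use an unadjusted analysis, so this is not the expected harm.
- The promised stratification factors might seem not to exist. Batch is one, and listing model covariates can properly be left to the analysis plan, which is not shown.
- Clinics might be thought to differ in services. Setting says the contrary: "Eligible clinics provide similar HIV care services including provision of ART". Only location and size carry the point, and even the urban/rural sentence describes the region's communities, not the 26 recruited clinics.

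There is also a practical objection. Recruitment is staggered, and the article does not say whether all 26 clinics are fixed before the first batch is allocated. If they are not, a limit across all clinics cannot be applied in one draw, and a tight limit in the batch of 6 would over-restrict it. This shapes the fix but does not remove the point.

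**Conclusion.** The point holds as a cheap design improvement, not as an error. The allocation ignores two clinic characteristics that the trial already records, and moderate imbalance on at least one such characteristic can be expected in roughly a third of draws. Given the planned adjustment, constraining the draw is worth about 1.5 to 2 points of power, together with arms that look alike at clinic level. These sizes rest on the assumed 8-of-26 split, the assumed 25% to 50% variance share and equal clusters of 20. The article does not show that location or clinic size predicts the MOS-HIV score; if neither does, the power gain disappears and only the balance remains.

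**What to change.** In the exclusion step of Site selection and randomisation, also drop allocations in which the arms differ, across all 26 clinics, by more than a stated limit on urban/rural location (for example, two clinics) or on log number of registered patients (for example, 0.25 SD). Then draw one at random from the rest, as now planned.

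If batches are drawn in sequence, apply the limits to the cumulative imbalance, with only a loose limit in the batch of 6. For batches already allocated, leave the allocation alone and rely on adjustment.

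In the primary model, include batch and the constrained clinic factors as covariates, so that analysis matches allocation.

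The cost is a few lines in the existing Stata code and a sentence in each of the two sections. The price is fewer allowable allocations (about a third remain under the example limits) and one or two clinic-level degrees of freedom. The sample size is unchanged.
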